#### Aim 1 Analysis

To study the short-term effect of the intervention on the primary outcome (pain intensity) and secondary outcomes (stress intensity and opioid use), all of which are measured daily, we will use linear mixed effects models. Fixed effect terms in the models include the group variable to represent the treatment effect and baseline outcome measurement. Participant-specific random effect terms will be used to account for within-participant correlation in repeat measures. Note that we do not include the time variable in our models because we are primarily interested in the treatment effect on the average pain, stress, and opioid use over time. We do not anticipate significant time trends, but will explore them in the secondary analysis.

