**Methods:**

A randomized controlled trial of the short-term (8 weeks) and long-term (6 months) effects of YCWS on stress, pain, and opioid use will be conducted with 170 adults with SCD. Patients will be randomized based on 1:1 ratio (stratified on pain intensity [≤5 or >5]) to be either in the experimental (self-monitoring of outcomes, alerts or reminders, and use of YCWS [relaxation and distraction exercises and support]) or control (self-monitoring of outcomes and alerts or reminders) group. Patients will be asked to report outcomes daily. During weeks 1 to 8, patients in both groups will receive system-generated alerts or reminders via phone call, text, or email to facilitate data entry (both groups) and intervention use support (experimental). If the participant does not enter data after 24 hours, the study support staff will contact them for data entry troubleshooting (both groups) and YCWS use (experimental). We will time stamp and track patients’ web-based activities to understand the study context and conduct exit interviews on the acceptability of system-generated and staff support. This study was approved by our institutional review board.

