### Randomization

We will use permuted block randomization with stratification based on worst pain intensity (≤5 or >5) to assign the 195 consecutively selected patients to the 2 study groups. The assignment will be blind until a sealed electronic envelope is opened after the patient completes the pretest data collection procedures.

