### Outcome Measures

#### Primary Outcome (Pain)

*Pain*, the primary outcome, will be measured using the pain intensity scale. This 3-item scale asks patients to report their current, least, and worst pain intensity in the past 24 hours on a scale of 0 (no pain) to 10 (pain as bad as it could be). We will calculate the average of the 3 scores to obtain an average pain intensity score, which has an internal consistency (*α*) of .85 [62] and predictive validity ([name], unpublished data, April 2022) in the population with SCD.

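### Low severity: the Aim 1 and Aim 2 models omit the worst-pain randomisation stratum, which leaves the stress and opioid-use tests slightly conservative if pain is prognostic

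*Protocol article*

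**What the plan says.** Randomization section: allocation uses "permuted block randomization with stratification based on worst pain intensity (≤5 or >5". The abstract gives a 1:1 ratio and a shorter name for the factor, "stratified on pain intensity [≤5 or >5".

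Aim 1 Analysis (weeks 1 to 8; pain, stress and opioid use): "Fixed effect terms in the models include the group variable to represent the treatment effect and baseline outcome measurement". Participant-specific random effects are added, and the section explains why time is left out. Aim 2 Analysis (months 3 to 6) lists the same fixed effects. Neither section mentions the stratum.

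Primary Outcome (Pain): "This 3-item scale asks patients to report their current, least, and worst pain intensity in the past 24 hours", and "We will calculate the average of the 3 scores to obtain an average pain intensity score". The baseline covariate in the pain model is therefore a mean that has worst pain as one of its three items. The corresponding covariate for stress is baseline stress, and for opioid use it is baseline opioid use.

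The Background describes the association between stress and pain as small to medium. The section on current drug therapy links high opioid doses with pain on most days, but gives no correlation.

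**The concern.** Stratified blocks force the arms to be nearly balanced on worst pain. If worst pain predicts the outcome, the treatment difference varies less from trial to trial than under simple randomisation. A model without the stratum, or a good proxy for it, does not credit that balance. It leaves the stratum's variance in the residual and reports a standard error that is too large. Confidence intervals are then wider than they need be, the true type I error falls below nominal, and some power is given away.

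The stress and opioid-use models are the exposed ones, because neither carries a pain variable. That makes four comparisons, two outcomes in each of two periods, all secondary and tested at 0.05.

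**Working it through.** **The plan's own figure.** The protocol gives no figure for this point. Its one power statement (Sample Power: SD 3, difference 1.5, two-sided 0.025, 170 patients) uses no covariates. With 85 per arm, 1.5 / (3 × √(2/85)) = 3.260 and Φ(3.260 − 2.241) = 84.6%, against the stated 80%. That gap is on the safe side and has nothing to do with the stratum.

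**Step 1. Does each model contain the stratifier?**

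| Outcome | Baseline covariate | Pain information in the model |
|---|---|---|
| Pain | mean of current, least, worst | yes; worst pain is one of the three items |
| Stress | baseline stress | none |
| Opioid use | baseline opioid use | none |

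**Step 2. Formulas.** Let W be baseline worst pain, S the indicator W > 5, B the baseline outcome and Y the participant's mean follow-up outcome. Let p be the share of patients with W > 5.

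- Loss from dichotomising: d = φ(z₁₋ₚ) / √(p(1−p)). This is 0.759 at p = 0.7 and 0.798 at p = 0.5.
- r_SB = d × r_WB and r_SY = d × r_WY.
- Share of residual variance explained by S after B: R² = (r_SY − r_SB × r_BY)² / [(1 − r_SB²)(1 − r_BY²)].
- Ratio of the standard error without the stratum to that with it: k = 1/√(1 − R²).
- True type I error at nominal 5%: 2Φ(−1.96k).

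The correlations, r_BY (0.3 to 0.7) and p (0.5 to 0.7) are assumptions. The protocol gives only the verbal description of the stress-pain association, read here as r = 0.1 to 0.3.

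**Step 3. Stress.** Worked case with r_WB = r_WY = 0.3, r_BY = 0.5, p = 0.7: r_SB = r_SY = 0.2276. The numerator is (0.2276 × 0.5)² = 0.01295 and the denominator is (1 − 0.0518) × 0.75 = 0.7112. So R² = 0.0182 and k = 1.009.

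| r_WB | r_WY | r_BY | p | R² | SE too wide by | True alpha |
|---|---|---|---|---|---|---|
| 0.1 | 0.1 | 0.5 | 0.7 | 0.2% | 0.1% | 4.98% |
| 0.3 | 0.3 | 0.7 | 0.7 | 1.0% | 0.5% | 4.9% |
| 0.3 | 0.3 | 0.5 | 0.7 | 1.8% | 0.9% | 4.8% |
| 0.3 | 0.3 | 0.3 | 0.5 | 3.3% | 1.7% | 4.6% |
| 0.5 | 0.5 | 0.5 | 0.7 | 5.6% | 2.9% | 4.4% |
| 0.3 | 0.5 | 0.5 | 0.7 | 9.9% | 5.4% | 3.9% |
| 0.3 | 0.5 | 0.3 | 0.7 | 11.2% | 6.1% | 3.7% |

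The first four rows fit a small to medium association; the last three go beyond it. For an effect with nominal 80% power, the fourth row gives Φ(0.8416k) = 80.4% without the stratum and Φ(2.8016k − 1.96) = 81.3% with it, a gain of 0.9 points.

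**Step 4. Check by simulation.** Setup: stratified permuted blocks (block size 4, assumed), 170 patients, 4,000 replicates, participant-mean outcomes analysed with and without the stratum. The standard-error ratio was 1.001 at r = 0.1; 1.005 to 1.010 at r = 0.3; 1.029 at r = 0.5; and 1.053 to 1.062 when pain correlates 0.5 with follow-up but 0.3 with baseline. This agrees with the formula. The simulated rejection rates carry a Monte Carlo error of √(0.05 × 0.95/4000) = 0.34 points, so the ratios are the better guide.

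**Step 5. Pain.** The stated alpha of .85 for three items implies a mean inter-item correlation of 0.85 / (3 − 2 × 0.85) = 0.654. Worst pain then correlates √((1 + 2 × 0.654)/3) = 0.877 with the three-item mean. If baseline pain predicts follow-up pain through that mean, or through the common level behind the three items, then r_WY = 0.877 × r_BY. The numerator of R² is then zero. Simulation gives a ratio of 0.999; the shortfall from 1 is the degree of freedom spent.

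**Step 6. Opioid use.** The formula is the same, but the protocol supplies no correlation to put in it. Only the direction can be stated.

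**The case against.** Three arguments favour leaving the plan alone.

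First, both sections say that the fixed effects include group and baseline, which need not be a complete list. The document is a journal article, and the analysis plan, which may name the stratum, is not shown. This has some force: nothing says that the stratum is excluded. But Aim 1 goes on to justify leaving out time, so the list reads as a deliberate specification, and as written it does not match the randomisation.

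Second, the harm is small, falls only on secondary outcomes and is in the safe direction. This stands and sets the severity.

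Third, a reader might infer more than the documents support:

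- *That standard errors are too wide for every outcome, including the primary one.* The baseline pain mean contains worst pain, so the pain model loses practically nothing.
- *That the stratum explains 5% to 20% of residual variance in stress or opioid use, with true type I error down to 2.8%.* The assumptions that fit a small to medium association give at most about 3%. With equal correlations and an even split, 10% needs r of about 0.5 to 0.76 and 20% needs about 0.66 to 0.92.
- *That the abstract contradicts the Randomization section on the stratifier.* The abstract's wording is a shortened form of worst pain intensity. The averaged score has its own name, and the Randomization section is specific.

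**Conclusion.** The concern holds in a narrow form. The stratification factor is absent from the stated Aim 1 and Aim 2 models. For stress and opioid use nothing stands in for it, so if pain is prognostic their standard errors are slightly too wide and their tests slightly conservative.

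For stress the excess is about 0.1% to 2% with assumed correlations of 0.1 to 0.3, and about 3% to 6% with stronger ones around 0.5. For opioid use the size is unknown. For pain it is practically nil. Omitting the stratum causes no bias and no inflation of type I error.

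The direction is firm. The sizes rest on assumed correlations, an assumed share of patients above the cut, and an analysis of participant means in place of the daily mixed model. The point is a free improvement of low severity, not a threat to the trial's conclusions.

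**What to change.** In Aim 1 Analysis and Aim 2 Analysis, add the randomisation stratum (worst pain ≤5 versus >5, coded as recorded by the randomisation system) to the fixed effects. It matters chiefly for stress and opioid use; include it in the pain model for consistency. Adding baseline average pain to the stress and opioid models is optional, as the stratified design does not call for it.

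The cost is one sentence and one degree of freedom per model. The variable must be known before allocation, so it should be available for every randomised patient. Fix the change before treatment groups are compared.

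Writing worst pain wherever the stratifier is named, including the abstract, would be a harmless tidying step.

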We will provide experimental group members access to 3 video banks from which they can choose their daily intervention. Patients will use only basic videos during week 1 to become familiar with the intervention and learn deep breathing and relaxation exercises through instructions. For example, one of the basic video clips entitled *Breathing out worry, breathing in light* guides the patients to “Notice the cloud-like formations on the screen. Observe how the images drift and change. As you breathe deeply, let your concerns and tensions (which worry you go) out into the atmosphere where they can dissolve just as the cloud-like formations on the screen dissolve and vanish from view. It is all right to let go of your worries. In fact, it is important to your health that you do so. Just breathe out problems and worries. See them drift off, walking by, and off the screen, no longer a part of you. Now, breathe in sunshine and healing energy.” This requirement is critical and supported by recent evidence showing that the respiratory control center communicates directly with and controls a brain center linked to attention, arousal, and panic [56]. [name] et al [57-60] ([name], unpublished data, January 2022) used these approaches in psychoneuroimmunology studies in patients with cancer or HIV, and we used them in our feasibility studies in patients with SCD. Some of the active components in the basic videos include colorful images similar to smoke or other nature images that slowly change shape against a dark background (images that do not represent any concept with known negative connotations), soothing female or male voice, deep breathing exercise, and slow-paced guided relaxation and distraction instructions. During weeks 2 to 8, patients will also have access to everyday videos and favorite videos.

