### Statistical Analysis

#### Overview

The study biostatistician will perform data management and analysis in collaboration with the PI and coinvestigators. The data will be stored in an SQL database and exported to the statistical software R for analysis. We will use an intention-to-treat approach, which includes all randomized participants in our analysis. We will consider *P*<.025 as statistically significant for intervention efficacy tests (short term and long term) on the primary outcome of pain intensity. For other inferences, we will consider *P*<.05 to be statistically significant. We will compute descriptive statistics (frequencies, means, SDs, etc) of baseline patient characteristics data, including demographics, pain, stress, and analgesic use before the test and compare the control group and the experimental group using chi-square tests or 2-tailed *t* tests. We expect no significant difference between the 2 randomly generated groups.

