#### Aim 2 Analysis

To estimate the long-term effects of the intervention, we will again use linear mixed effects models. Fixed effect terms in the models include the group variable to represent the treatment effect and baseline outcome measurement. Participant-specific random effect terms will be used to account for within-participant correlation in repeat measures.

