#### Missing Data

Random effect models can accommodate longitudinal data with missing visits. For visits with partial data (item-level missing data), we will use multiple imputation by fully conditional specification to generate multiple completed data sets, on each of which statistical inference will be performed separately and then aggregated using Rubin rule [72]. This allows us to fully use the information provided by the participants.

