#### Sample Power

The success of this study lies on its short-term and long-term efficacy on the primary outcome of pain intensity. We conservatively assume an SD of 3 for pain intensity based on values we observed in earlier studies. With a 2-sided type I error of 0.025, the proposed sample of 170 patients provides 80% power to detect a pain reduction of 1.5, below the minimal pain reduction of 2, which is considered as clinically meaningful.

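### Leaving time out of the Aim 1 mixed model makes the 8-week pain effect an average over reported days, which can be biased if the effect builds up, or if pain trends and loss differs by arm

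*Protocol article*

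**What the plan says.** Aim 1 Analysis fits linear mixed models to daily pain, stress and opioid use. The fixed effects are group and baseline outcome, with participant random effects. It adds: "Note that we do not include the time variable in our models because we are primarily interested in the treatment effect" on average levels over time. It then says: "We do not anticipate significant time trends, but will explore them in the secondary analysis".

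Aim 2 Analysis lists the same terms: "To estimate the long-term effects of the intervention, we will again use linear mixed effects models". It does not say which days enter the model. Study Aims and Hypotheses places the long-term hypothesis in months 3 to 6.

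Missing Data says: "Random effect models can accommodate longitudinal data with missing visits". Multiple imputation is planned only for item-level gaps within a visit.

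Overview says: "We will use an intention-to-treat approach, which includes all randomized participants in our analysis". It tests short-term and long-term pain at P<.025 each. Sample Size plans for 13% attrition, with 170 of 195 participants retained at 8 weeks.

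**The concern.** A mixed model handles missing days under missing-at-random only if its mean over time is right. With group and baseline alone, the model treats pain as flat and the effect as constant. If either changes, a participant who stops in week 3 contributes a three-week average to something labelled an eight-week average.

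The design gives some reason to expect change:
- **Effect.** In the experimental arm, "Patients will use only basic videos during week 1 to become familiar with the intervention", and the other video banks open in weeks 2 to 8. An effect that grows as participants learn the exercises is plausible.
- **Pain.** Eligibility requires pain above 3 in the previous 24 hours, so some common decline through regression to the mean is possible.

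At stake is the size of the primary short-term estimate, which readers will set against the 2-point reduction that Sample Power calls clinically meaningful.

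**Working it through.** **The plan's own figure.** Sample Power states: "With a 2-sided type I error of 0.025, the proposed sample of 170 patients provides 80% power to detect a pain reduction of 1.5", and "We conservatively assume an SD of 3 for pain intensity". With 85 per arm, the standard error is 3 × √(2/85) = 0.460 and 1.5/0.460 = 3.26. Subtracting the critical value 2.24 leaves 1.02, so power is 84.6% (84.0% with the t distribution). The stated 80% is therefore conservative, and nothing below depends on it.

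**Inputs.** From the document: 170 participants, SD 3, difference 1.5, 13% attrition, 8 weeks (56 days). Assumed, because the document gives no values: intraclass correlation 0.6, the size and shape of any trend, an effect that builds linearly, dropout spread evenly over the 8 weeks, and the split of loss between arms.

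**Why the estimate follows the reported days.** The variance is 9, of which 5.4 is between and 3.6 within participants. After baseline adjustment the between-participant part is 5.4 × (1 − 0.6) = 2.16, against 3.6/56 = 0.06 for the mean of a complete diary. Participants therefore get nearly equal weight, each with the mean of whatever days they reported.

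**Hand calculation.** Let time run from 0 to 1 over the 8 weeks, with dropouts stopping on average at 0.5.
- *Building effect*, 2 × (−1.5) × t, which averages −1.5. A participant stopping at s shows −1.5 × s, so dropouts average −0.75. Bias ≈ 0.75 × (dropout proportion in the experimental arm).
- *Common decline* of 1.5 points. Completers average −0.75 and dropouts −0.375. Bias ≈ 0.375 × (experimental dropout − control dropout), which is zero when loss is equal.

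**Against simulation** (600 trials per row, Monte Carlo error about 0.01; positive means benefit understated; dropout given as control/experimental):

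| Scenario | Hand calculation | Simulated, no time | Simulated, time and group-by-time |
|---|---|---|---|
| No trend, constant effect, 13%/13% or 13%/30% | 0 | 0.00 | 0.00 |
| Decline 1.5, constant effect, equal 13% or 32% | 0 | 0.00 or −0.01 | 0.00 or −0.01 |
| Decline 1.5, constant effect, 5%/21% | 0.375 × 0.16 = 0.06 | 0.05 | 0.00 |
| Decline 1.5, constant effect, 15%/45% | 0.375 × 0.30 = 0.11 | 0.11 | 0.00 |
| Building effect, equal 13% | 0.75 × 0.13 = 0.10 | 0.09 | 0.00 |
| Building effect, equal 32% | 0.75 × 0.32 = 0.24 | 0.22 | 0.00 |
| Decline 1.5 and building effect, 15%/45% | 0.75 × 0.45 + 0.11 = 0.45 | 0.43 | 0.01 |

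Simulated values fall slightly below the hand values because short diaries get a little less weight. Replacing linear time with weekly terms and group-by-week also removed the bias, and the standard error did not rise.

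**Aim 2, only if the model is fitted to months 3 to 6 alone.** Assume a correlation of 0.8 between weeks 1 to 8 and months 3 to 6, and loss before month 3 of about 13% to 32%. Negative means benefit overstated.
- Loss unrelated to pain: bias about 0.
- Loss related to earlier pain in the same way in both arms: +0.05 to +0.07.
- High-pain participants lost in the experimental arm only: −0.13 to −0.27.
- Opposite patterns in the two arms: −0.20 to −0.46.

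Using the weeks 1 to 8 data reduces all of these to 0.02 or less in size.

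**The case against.** The best defence is that the article names its target, the average over time, and that the simple model estimates it correctly under several ordinary conditions. It also promises to explore trends. In weeks 1 to 8 both arms receive daily reminders and staff contact after 24 hours without data, so heavy loss is not what the document foresees. Regression to the mean acts in both arms and biases the contrast only if loss differs. The basic-videos period is one week of eight. At 13% equal attrition even a fully building effect costs about 0.1 of 1.5 points. In every simulated row with a true effect, the test still rejected in at least 99.5% of trials, so detection was not threatened there.

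Most of this stands, and it limits the size of the point. It does not justify the omission, because the same average can be had as a contrast from a model that contains week. Exploring trends afterwards leaves the primary estimate as it was.

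A reader might infer three stronger things that the document does not support:
- *Losing daily data biases the estimates in itself.* It does not: the first two rows of the table show no bias.
- *Type I error is seriously inflated.* A rate of 21% against 2.5% appeared only with an assumed 3-point decline and 35% against 10% early dropout. With a 1.5-point decline and 15%/45% loss it was 3.2% in 1,000 trials, where the Monte Carlo error is √(0.025 × 0.975/1000) = 0.5 percentage points.
- *Aim 2 contradicts the intention-to-treat statement.* That requires assuming that only months 3 to 6 are fitted. The article does not say so, and the full protocol or analysis plan may settle it.

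**Conclusion.** The point holds in conditional form. Omitting time is a stated choice, and the missing-data approach rests on the model it weakens. The short-term pain effect can be biased if the treatment effect changes over the 8 weeks, or if pain trends and loss differs by arm.

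Under the assumptions above, the benefit is understated by about 0.1 points (0.09/1.5 = 6%) at the planned attrition with a building effect. This rises to about 0.4 points (0.43/1.5 = 29%) with a trend, a building effect and 15%/45% loss, which is far heavier than the document plans for. The direction is not fixed: with a declining trend, greater loss in the control arm would overstate the benefit.

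For Aim 2 the point extends only conditionally, because the data window is not stated. This is an inexpensive improvement to the plan, not a flaw that invalidates the trial.

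**What to change.** In Aim 1, add study week (categorical) and group-by-week to group, baseline outcome and participant random effects. Define the short-term effect as the equally weighted average of the weekly group contrasts over weeks 1 to 8. This answers the question the article already asks.

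Use the same form for Aim 2, with the contrast averaged over months 3 to 6. If only those months would otherwise be fitted, keep weeks 1 to 8 in the same model, with participant effects that may differ between the periods but correlate. Participants lost before month 3 then still contribute.

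The sentence about not anticipating time trends can stay: it states an expectation, and the revised model no longer depends on it.

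The cost is analysis wording and more model parameters. No new data are needed, and simulation showed no loss of precision.
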